     1. HLA matching: Allogeneic UCBCs will be obtained from BMDI Cord Blood Bank with an HLA matching of at least 4/6. As HLA matching and processing UCBCs may be time-consuming, the eligibility (neuroimaging) will be reconfirmed before administering the allogeneic UCBCs after successful HLA matching.
     2. Age of administration: Allogeneic UCBCs will be administered via IV infusion anytime from birth until three months of life, generally within 2-3 weeks of diagnosis of confirmed severe preterm brain injury.
     3. Cell infusion: Only one allogeneic UCBC infusion will be administered intravenously.
     4. UCBC dose: The infusion is aimed for 50 million total nucleated cells (TNCs) per kilogram of body weight will be administered. This therapeutic dose is based on preclinical^30^ and clinical studies^5,6^ of UCBC for different types of perinatal brain injury.
     5. Route: The UCBCs will be administered intravenously via a peripheral intravenous cannula.
  2. ***Comparison***

There will be no control group as this is a single-arm, open-label, phase-I study.

- 1. ***Outcomes***
     1. Primary outcomes
        1. Feasibility: Allogeneic UCBC therapy will be considered feasible if there is an availability of at least 4/6 HLA-matched allogeneic UCBCs sourced from the BMDI Cord Blood Bank for >60% of eligible infants.
        2. Safety: Allogeneic UCBCs will be considered as safe if there are no serious adverse events related to UCBCs during and for 48 hrs post-infusion and the absence of GVHD in the first three months after cell infusion. The safety outcomes will be reported for eligible infants where feasibility is demonstrated, and allogeneic UCBCs are administered.
     2. Secondary outcomes
        1. Clinical outcomes: The following clinical outcomes will be reported for the infants who received infusion.
           1. Death, until 24 months of corrected age
           2. Moderate to severe bronchopulmonary dysplasia, assessed as oxygen or positive pressure requirement at 36 weeks of postmenstrual age
           3. Severe retinopathy of prematurity, assessed as any retinopathy requiring anti-VEGF or laser treatment before discharge
           4. Necrotising enterocolitis, assessed as bell stage 2 or more before discharge
           5. Culture-proven sepsis, bacterial or fungal, requiring antibiotics treatment for 7 or more days before discharge

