At three months corrected age: General movements assessment and Hammersmith infant neurological examination

At 12 months of corrected age: Gross Motor Function Measure-66 and Infant–toddler Social and Emotional Assessment

At two years of corrected age: Bayley Scales of Infant and Toddler development-IV, and medical assessment for disability

- - - 1. Relevant laboratory tests will be performed to monitor the response and to detect any adverse events, such as GVHD

Before the infusion: Cytokine analysis, including interleukin 1b (IL-1b), IL-6, Tumour Necrosis Factor (TNF-α) and IL-10

24 h after the infusion: Cytokine analysis, full blood examination (FBE), chimerism assessment and LFTs

4 day, 1 week and 1 month chimerism assessment

1 week, 1 month and 3 months post-transfusion: FBE and LFTs

Chimerism assessment will be repeated at 3 months if there are detectable donor cells at 1 month testing (optional assessment)

Lymphocyte subset analysis will also be performed if white cell count is low, which is consistent with GVHD

- - 1. **Data Safety Monitoring Board (DSMB)**: A DSMB consisting of a neonatologist, and paediatric neurologist or cell therapist or haemato-oncologist will be established to review all the adverse events. All serious events will be reported to DSMB within 7 days of occurrence.
       - 1. *Interim analysis:* DSMB will be requested to conduct an interim analysis following the enrolment of five patients in each group to assess the feasibility and adverse events. DSMB and HREC will also review whenever there is a serious event to ensure it is safe to continue the trial.
         2. *Criteria for premature termination of trial*: DSMB and HREC will be consulted for an independent review of trial conduct, progress and any serious events related to cell therapy, which will further determine whether the trial requires premature termination. No predetermined interim analysis will be conducted. The analysis will only be conducted after at least 10 infants have been recruited in each stratum.
    2. Reporting:
       1. Any events occurring after the allogeneic UCBC therapy will be reported to the relevant parties. Events will be categorised as per the National Health and Medical Research Council 2016 recommendation^31^ and report any related or unrelated events

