**Adverse event (AE)**: Any untoward medical occurrence in a patient or clinical trial participant administered a medicinal product and that does not necessarily have a causal relationship with this treatment.

**Adverse Reaction (AR)**: Any untoward and unintended response to an investigational medicinal product related to any dose administered.

**Serious AE/AR (SAE/SAR)**: Any adverse event/adverse reaction that results in death, is life-threatening, requires hospitalization or prolongation of existing hospitalization, or results in persistent or significant disability or incapacity.

**Suspected Unexpected Serious Adverse Reaction:** An adverse reaction that is both serious and unexpected.

- - - 1. **HREC**: Any SAE/SAR will be reported to the DSMB and HREC within 7 days of occurrence Protocol amendments, annual research progress and safety reports will be submitted to the HREC as needed. Any protocol deviations and breaches will be investigated by the principal investigator and shall be reported to the HREC.
  1. **Data management**
     1. Data collection: The data from electronic medical records will be recorded on a paper case reporting form OR electronic database (REDCAP). The paper records will be stored in a locked filing cabinet, and the electronic records will be secured with secure password protection.
     2. Data retention: The records will be retained securely for 25 years following completion of the study as per Health Records Act 2001, VIC, Act Number 2/2001.
  2. **Participants' reimbursement**: Costs relevant to this trial will be reimbursed. This includes travel for treatment or follow-up, accommodation and meals expenses, and parking costs. All trial treatments, including hospital admission, are provided free of charge.
  3. **Financial disclosure and conflicts of interest:** [name] receives a doctoral scholarship from Monash University and Lions Cord Blood Foundation. Profs [name] and [name] receive funding from the National Health and Medical Research Council of Australia. The study will also be supported by funds from the Monash Health Foundation. The funding bodies have no role in the design of the study. They will also have no role in data collection, analysis, and interpretation of data and dissemination of the results.

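### Non-serious GVHD would fail the primary safety outcome, yet it triggers neither the 7-day report to the DSMB and HREC nor their review of whether to continue

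*Combined protocol and SAP*

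**What the plan says.** Outcomes, Primary outcomes: the safety outcome has two limbs. One is no serious adverse event related to the cells during infusion or in the next 48 hours. The other is "absence of GVHD in the first three months after cell infusion". The seriousness condition belongs to the first limb only.

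Safety monitoring and reporting, Data Safety Monitoring Board: "All serious events will be reported to DSMB within 7 days of occurrence". The HREC item under Reporting repeats the clock: "Any SAE/SAR will be reported to the DSMB and HREC within 7 days of occurrence". The Interim analysis item adds the event-driven review: "DSMB and HREC will also review whenever there is a serious event to ensure it is safe to continue the trial". The item on premature termination says that the two bodies will be consulted on trial conduct, progress and "any serious events related to cell therapy, which will further determine whether the trial requires premature termination". It states no criterion and does not name GVHD.

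An event is serious if it "results in death, is life-threatening, requires hospitalization or prolongation of existing hospitalization, or results in persistent or significant disability or incapacity". The Appendix gives the same definition in substance. Neither place makes GVHD serious by default.

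On membership, the protocol describes "A DSMB consisting of a neonatologist, and paediatric neurologist or cell therapist or haemato-oncologist", set up to review all adverse events. No timetable is given for that general review.

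**The concern.** The GVHD limb of the primary outcome and the oversight trigger use different thresholds. GVHD of any severity in the first three months means that the cells do not meet the protocol's definition of safe. The independent bodies are told promptly, and asked whether the trial may safely continue, only when an event is serious.

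Mild GVHD falls between the two. The acute features to be monitored include any red rash, vomiting and diarrhoea, jaundice and abnormal liver tests. An infant already in the neonatal unit could show one of these, be judged to have GVHD, and neither be in danger of life nor stay longer. The Risk-benefit analysis says that the occurrence and severity of GVHD in preterm infants are unknown. A first mild case is therefore the kind of early signal that a phase I safety trial exists to pick up. Under the stated rule, further infants could be enrolled and infused before any independent body had to look at it.

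**Working it through.** The protocol gives no figure to reproduce here. The check compares the rules and then counts infants.

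**Step 1: a mild GVHD case against each route.** Take GVHD in the first three months that meets no seriousness criterion.

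| Route | Condition | Applies to this case? | Deadline |
|---|---|---|---|
| Primary safety outcome | Any GVHD to three months | Yes: outcome failed | n/a |
| Report to DSMB (and HREC) | Serious event | No | 7 days |
| Event-driven DSMB/HREC review | Serious event | No | None stated |
| Consultation on premature termination | Related serious events; also conduct and progress | Not as an event | None stated |
| General DSMB review | All adverse events | Yes | None |
| Report of any event | Any event after infusion; recipients called only the relevant parties | Yes | None |
| Safety reports to HREC | Submitted with annual progress reports, as needed | Yes, in principle | No event clock |
| Interim look after five per group | Requested in one item; the next says no predetermined interim analysis will be done | Only if the look is held | Set by enrolment |

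The case fails the outcome and meets neither prompt trigger. What remains is untimed or contradicted elsewhere in the same section.

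**Step 2: how many infants could follow.** Inputs: at least 20 infants, 10 per stratum (Sample size), and a look after five in each group (Interim analysis). Assume that enrolment stops at exactly 20 and that the case occurs in the third infant enrolled, a position chosen for illustration.

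- Look held, balanced accrual: it falls at 5 + 5 = 10 enrolled. Infants after the third: 10 − 3 = 7.
- Look held, one stratum fills before the other reaches five: it falls at 10 + 5 = 15 enrolled. Infants after the third: 15 − 3 = 12.
- Look not held: analysis waits for 10 + 10 = 20. Infants after the third: 20 − 3 = 17.

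These are infants enrolled after the third infant. GVHD may appear at any time in three months, so some of them could already be enrolled when the case is recognised. Sample size also says that fewer infants may be infused than enrolled. All three counts are therefore on the high side for infants whose infusion a prompt report could have informed.

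**Step 3: how likely such a case is.** The documents give no rate. For an assumed rate p per infant, the chance of at least one case in 20 infused infants is 1 − (1 − p)^20:

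- p = 1%: 18.2%
- p = 2%: 33.2%
- p = 5%: 64.2%
- p = 10%: 87.8%

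This is context only. The protocol expects the risk to be minimal, and p here would have to be the rate of GVHD that meets no seriousness criterion, which is not known.

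**The case against.** The strongest reply is that the DSMB is not blind to mild GVHD. Its remit covers all adverse events, any event after infusion is to be reported, HREC receives safety reports, and an adverse-event look after five infants per group is requested. This stands. A reader might infer that non-serious GVHD never reaches the board, or that 17 further infants would certainly be infused without review. The documents support neither. The reply does not supply a deadline or a trigger, and the one scheduled look is denied in the next item.

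A second reply is that many GVHD cases would be serious anyway, since prolonged hospital stay is enough. That is correct, and it limits the gap to cases meeting no seriousness criterion. Events are also to be categorised under national guidance that is not among the documents, so what that guidance might add cannot be checked.

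A third reply concerns the board. A reader might infer from the membership line that no one on it will understand GVHD. The wording lets a neonatologist and a paediatric neurologist suffice, but it does not choose that pair, and either could have the relevant knowledge. No DSMB charter is in the documents. Lack of expertise is therefore a possibility that the wording leaves open, not a finding.

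Finally, the 3 to 5 years in the Synopsis might be turned into an infusion rate. The Synopsis does not say whether that period includes the 24 months of follow-up, so no rate is used here.

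**Conclusion.** The point holds as a mismatch between two stated rules. GVHD of any severity fails the primary safety outcome, but the 7-day report and the event-driven review cover serious events only, so a non-serious case reaches the DSMB by untimed or contradicted routes. Under the assumptions in the working, 7 to 12 infants could be enrolled between a case in the third infant and the interim look if it is held, and up to 17 could follow if it is not. The number infused may be smaller. The conclusion does not depend on any GVHD rate. It should be corrected because following the rule as written can delay independent review of a primary safety event, and the correction needs only wording.

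**What to change.** In the Data Safety Monitoring Board and Reporting items:

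1. Add suspected or confirmed GVHD of any severity to the events reported to the DSMB and HREC within 7 days.
2. Add the same events to those that prompt the DSMB/HREC review of whether it is safe to continue.
3. Reconcile the request for a look after five infants per group with the statement that no predetermined interim analysis will be done.

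Whether infusions wait for the DSMB's reply is for the sponsor and the DSMB to state; no rule is proposed here. The sponsor may also wish to confirm that the board includes haematology or cell-therapy expertise, since the membership wording does not assure it.

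The cost is protocol text, with matching charter text if a charter exists. Some extra reports should be expected, because rash, vomiting, jaundice and abnormal liver tests are non-specific and some suspected cases will prove not to be GVHD. The protocol should therefore say what makes a case suspected.

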**Consent**

**Blood** for HLA-typing/matching

**4/6-5/6 HLA-**matched UCBCs availability (***FEASIBILITY***)

Re-confirm **eligibility**

**INTERVENTION (Examine**, **blood** for cytokines, **administer UCBCs)**

**Blood** for cytokines (24 h) & assess for side effects (up to 48 h)

**Blood** for chimerism (4d)

**Blood** for FBE, LFTs and chimerism (1w, 1m)

**GVHD assessment** at 2 m

**Blood** (FBE/LFTs), & **GVHD assessment** (3m)(***SAFETY***)

**MRI** at TEA

**Assessments: Neurological** (3, 12, 24 m) and **GVHD** (6, 9, 12, 18, 24m)

**Table 1**: Safety, adverse events, and neurological outcome monitoring

| Timeline | Cardiorespiratory monitoring | Infection monitoring | Physical examination | Cytokine analysis | FBE*, chimerism assessment and LFT | Neurodevelopmental assessment | Neuroimaging |
| --- | --- | --- | --- | --- | --- | --- | --- |
| -2 to 0 h | √ | √ | √ | √ |  |  |  |
| 0 to 48 h | √ | √ |  |  |  |  |  |
| 24 h |  |  | √ | √ | √ |  |  |
| 4 d |  |  |  |  | √ (Chimerism only) |  |  |
| 7 d |  |  | √ |  | √ |  |  |
| 1 m |  |  | √ |  | √ |  |  |
| 2 m |  |  | √ |  |  |  |  |
| 3 m |  |  | √ |  | √ (Chimersim is optional) | √ (TEA) | √ (MRI at TEA) |
| 6 m |  |  | √ |  |  | √ (3 m CA) |  |
| 9 m |  |  | √ |  |  |  |  |
| 12 m |  |  | √ |  |  | √ (12 m CA) |  |
| 18 m |  |  | √ |  |  |  |  |
| 24 m |  |  | √ |  |  | √ (24 m CA) |  |

**Note**: CA, corrected age; FBE, full blood examination (*-lymphocyte subset analysis for patients with abnormal FBE consistent with GVHD, and chimerism analysis will be repeated at 3, 6 or 12 months if there are detectable donor cells at 1 and/or 3 months testing); LFT, liver function test; MRI, magnetic resonance imaging; TEA, term equivalent age

**ALLO Trial Case Report Form**

| **Study ID number** |  | |
| --- | --- | --- |
| **Name** | **DOB** | **Gender** M/F |
| **Birth weight (grams)** | **Gestational age at birth (weeks)** | |
| **Antenatal steroids x1 X 2** | **FGR** Y/N | |
| **Antenatal ultrasounds** | | |
| **Pregnancy complications** | | |
| **Mode of delivery** | | |
| **Apgar scores** | | |
| **Resuscitation –** None/Oxygen/CPAP/Mask PPV/Intubation/CPR/Adrenaline  **Resuscitation details** | | |
| **Surfactant/ MIST** | | |
| **Ventilation details** | | |
| **Echo/ PDA** | | |
| **IVH** Severe IVH Y/N  **PVL/ PVE** Cystic PVL Y/N  **Details of cranial ultrasound** | | |
| **Culture proven sepsis** | | |
| **Other diagnoses** | | |
| **Medications** | | |

**Details of care on day of UCBCs**

| **Date** | **Day of life** | | **Corrected gestation** | |
| --- | --- | --- | --- | --- |
| **Current Weight (date)** | | | | |
| **Current respiratory support** | | **Settings** | | **FiO2** |
| **Last cranial USS (date)** | | | | |
| **Last Echocardiogram (date)** | | | | |
| **Last serum chemistry (date)**  **FBE (date)** | | | | |
| **Medications** | | | | |
| **Feeds** | | | | |

**Vascular access, site**

**Time of administration (24h clock)**

**Volume of infusion (mL): Cell dose:**

**Monitoring on day of UCBC administration**

**Events (including investigations) in the first 48 hours**

**Local site** – Erythema/ Swelling/ Any other change_____________________

**Respiratory/ Cardiovascular**

| **Gas** | **pH** | **pCO2** | | **pO2** | **BE** | **HCO3** | **Lactate** | **OI** | **RSS** |
| --- | --- | --- | --- | --- | --- | --- | --- | --- | --- |
| **-1h** |  |  | |  |  |  |  |  |  |
| **Settings** |  | | | **MAP** |  | **FiO2** |  |  | |
| **Acceptable** |  | |  |  |  |  |  |  |  |
| **1h** |  |  | |  |  |  |  |  |  |
| **Settings** |  | | | **MAP** |  | **FiO2** |  |  | |
| **6h** |  |  | |  |  |  |  |  |  |
| **Settings** |  | | | **MAP** |  | **FiO2** |  |  |  |
| **Cessation of acceptable limits for gas** | | | | | | | | | |
| **12h** |  |  | |  |  |  |  |  |  |
| **Settings** |  | | | **MAP** |  | **FiO2** |  |  |  |
| **24h** |  |  | |  |  |  |  |  |  |
| **Settings** |  | | | **MAP** |  | **FiO2** |  |  | |
| **48 h** |  |  | |  |  |  |  |  |  |
| **Settings** |  | | | **MAP** |  | **FiO2** |  |  |  |

| **Time**  **(hrs)** | **-2** | **-1.75** | **-1.5** | **-1.25** | **-1** | **-0.75** | **-0.5** | **-0.25** | **0** | **Accept-able** |
| --- | --- | --- | --- | --- | --- | --- | --- | --- | --- | --- |
| **BP** |  |  |  |  |  |  |  |  |  |  |
| **HR** |  |  |  |  |  |  |  |  |  |  |
| **RR** |  |  |  |  |  |  |  |  |  |  |
| **Temp** |  |  |  |  |  |  |  |  |  |  |

| **Time**  **(hrs)** | **0** | | **.25** | | | | **.5** | | **.75** | | | **1** | | **2** | | **3** | **4** | | **5** | | **6** | | **7** | | **8** | | | **9** |
| --- | --- | --- | --- | --- | --- | --- | --- | --- | --- | --- | --- | --- | --- | --- | --- | --- | --- | --- | --- | --- | --- | --- | --- | --- | --- | --- | --- | --- |
| **BP** |  | | |  | |  | | |  | | |  |  | | |  |  | |  | |  | |  | |  | | |  |
| **HR** |  | | |  | |  | | |  | | |  |  | | |  |  | |  | |  | |  | |  | | |  |
| **RR** |  | | |  | |  | | |  | | |  |  | | |  |  | |  | |  | |  | |  | | |  |
| **Temp** |  | | |  | |  | | |  | | |  |  | | |  |  | |  | |  | |  | |  | | |  |
| **Time**  **(hrs)** | **10** | **11** | | | **12** | | | **13** | | **14** | **15** | | | | **16** | **17** | **18** | **19** | | **20** | | **21** | | **22** | | **23** | **24** | |
| **BP** |  |  | | |  | | |  | |  |  | | | |  |  |  |  | |  | |  | |  | |  |  | |
| **HR** |  |  | | |  | | |  | |  |  | | | |  |  |  |  | |  | |  | |  | |  |  | |
| **RR** |  |  | | |  | | |  | |  |  | | | |  |  |  |  | |  | |  | |  | |  |  | |
| **Temp** |  |  | | |  | | |  | |  |  | | | |  |  |  |  | |  | |  | |  | |  |  | |
| **Time**  **(hrs)** | **27** | **30** | | | **33** | | | **36** | | **39** | **42** | | | | **45** | **48** |  |  | |  | |  | |  | |  |  | |
| **BP** |  |  | | |  | | |  | |  |  | | | |  |  |  |  | |  | |  | |  | |  |  | |
| **HR** |  |  | | |  | | |  | |  |  | | | |  |  |  |  | |  | |  | |  | |  |  | |
| **RR** |  |  | | |  | | |  | |  |  | | | |  |  |  |  | |  | |  | |  | |  |  | |
| **Temp** |  |  | | |  | | |  | |  |  | | | |  |  |  |  | |  | |  | |  | |  |  | |

Comments:

| **Adverse event (including investigations)details** | **AE classification*** |
| --- | --- |
| **Respiratory** |  |
| **Cardiovascular** |  |
| **Haematologic** |  |
| **Renal** |  |
| **Neurological** |  |
| **Infection** |  |
| **Systemic** |  |
| **Other** |  |

*Refer to protocol

**Overall outcomes during nursery stay**

| **Days of ventilation** | **Invasive** | | **Noninvasive** |
| --- | --- | --- | --- |
| **Days to room air** | **Home oxygen**  Y/N | | **Amount** |
| **Length of stay** | | **Referral to NDIS** | |
| **Term MRI brain** | | | |
| **Other morbidities or outcomes relevant to the study before discharge (please give details)**  **FEASIBILITY: Y/N HLA Matching: 4/6, 5/6, 6/6 HLA Loci matched:**  **SAFETY: Y/N**  **Necrotising enterocolitis**  **Culture proven late onset sepsis**  **Bronchopulmonary dysplasia**  **ROP**  **Intraventricular haemorrhage**  **Comments** | | | |
| **Neurodevelopment testing during admission**  **General Movements**  **HINE** | | | |
| **Medications on discharge** | | | |

| **Death before nursery discharge**  **Cause of death** |
| --- |

**GVHD Assessment and bloods**

| **Trial** | **ALLO-Trial** | | | | | | | |
| --- | --- | --- | --- | --- | --- | --- | --- | --- |
| **Patient ID** |  | | | | | | | |
| **Review** | **Time point** | **General condition** | **Laboratory evaluation** | **Skin** | **Liver** | **GIT** | **Chimerism** |  |
| **0** | Pre-infusion |  |  |  |  |  | N/A |  |
| **1** | 24 hours post |  |  |  |  |  |  |  |
| **2** | 1 week |  |  |  |  |  |  |  |
| **3** | 1 month |  |  |  |  |  |  |  |
| **4** | 2 month |  |  |  |  |  |  |  |
| **5** | 3 month |  |  |  |  |  |  |  |
| **6** | 6 month |  |  |  |  |  |  |  |
| **7** | 9 month |  |  |  |  |  |  |  |
| **8** | 12 months |  |  |  |  |  |  |  |
| **9** | 18 months |  |  |  |  |  |  |  |
| **10** | 24 months |  |  |  |  |  |  |  |

**Follow up till 2 years of age**

| ***Term equivalent age (date)*** |
| --- |
| **Physical examination** |
| **Growth parameters** |
| **Development (TEA)**  **GMA**  **HNNE**  **Comments** |

| ***3 months of corrected age(date)*** |
| --- |
| **Physical examination** |
| **Growth parameters** |
| **Development**  **GMA**  **HINE**  **Comments** |

| ***12 months of age(date)*** |
| --- |
| **Physical examination** |
| **Growth parameters** |
| **Development**  **GMFM-66**  **Infant-toddler social emotional assessment**  **Comments** |

| ***24 months of age(date)*** |
| --- |
| **Physical examination** |
| **Growth parameters** |
| **Development (BSID IV)**  **Medical assessment of disability**  **Comments** |

*As clinically indicated

